### Interim analysis

An interim analysis will be performed 6 months after 150 patients have been included. The interim analysis will be performed on the safety population and the actual treatment group will be unblinded to the independent statistician. All patients who are accrued and treated will be included in the analysis. Events of patients who are lost to follow-up, or who do not have 6 months of follow-up, will be included. The difference between groups in proportion of patients with events at 6 months of follow-up will be tested by means of a one-sided Fisher exact test for differences in independent binomial proportions. The data safety monitoring board will use the following stopping rule: If there is a significant difference in MACE between the two groups the trial will be stopped (one-sided test, alpha = 0.05).

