## Statistical analysis

### Sample size calculation and statistical power analysis

The event rates for both groups were defined as follows:

In the usual care group, the event rates are estimated based on data from our previous all-comers registry [7] and the SMILE trial [13]. Rates of MACE in the ischaemia driven group are estimated based on the results of the SMILE trial [13].

In order to assess the superiority of MV-PCI over IRA-PCI, we assume the incidence of MACE to be 20% in the IRA-PCI group and 10% in the ischaemia-driven MV-PCI group. On the basis of a two-sided test size of 5% and a power of 80%, it is calculated that a minimum of 197 patients is needed to be recruited in each group to detect a 10% difference in the incidence of MACE at 1 year. To account for 5% loss to follow-up, a total of 414 (394/0.95) patients will be recruited.

The primary analysis is an intention-to-treat analysis of all randomised patients. A per-protocol analysis will also be performed. All continuous variables will be expressed as mean ± SD and analysed by the Student’s *t*-test. Categorical variables will be analysed by the chi-square or Fisher exact test, as appropriate. Baseline variables with non-Gaussian distributions will be compared using the Mann-Whitney U test and summarised with medians and interquartile range. For the primary endpoint and its components, 95% confidence intervals will be reported. The event-free survival curve for MACE will be constructed using the Kaplan-Meier method, and statistical differences between curves will be assessed by the log-rank test. The hazard ratio for treatment comparisons will be estimated using Cox proportional hazard models. Mean scores of the health-related quality of life will be compared between groups using the independent *t*-test. Statistical analysis will be performed with SPSS (version 15.0, SPSS, Chicago, IL, USA). An independent endpoints committee blinded to the randomisation group will adjudicate clinical study endpoints.

Descriptive analyses of primary outcomes will be performed for the following pre-specified subgroups:Diabetic patients versus non-diabetic patientsElderly (≥75 years) versus young patients (<75 years)Male versus female genderHigh- (GRACE >140) versus low-risk (GRACE ≤140) patients according to Global Registry of Acute Coronary Events (GRACE) risk scorePatients with previous myocardial infarction versus patients with no previous myocardial infarction

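### The interim MACE stopping test uses the safety population, not all randomised patients by arm, and counts short follow-up in a 6-month proportion

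*Protocol article*

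**What the plan says.** The protocol article sets one analysis population for the final result and another for the decision to stop.

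- **Sample size calculation and statistical power analysis:** "The primary analysis is an intention-to-treat analysis of all randomised patients".
- **Interim analysis, population:** "The interim analysis will be performed on the safety population and the actual treatment group will be unblinded to the independent statistician". The next sentence adds: "All patients who are accrued and treated will be included in the analysis".
- **Interim analysis, timing and follow-up:** "An interim analysis will be performed 6 months after 150 patients have been included". On incomplete follow-up: "Events of patients who are lost to follow-up, or who do not have 6 months of follow-up, will be included".
- **Interim analysis, test:** the between-group difference in the proportion with events at six months "will be tested by means of a one-sided Fisher exact test for differences in independent binomial proportions".
- **Interim analysis, consequence:** "If there is a significant difference in MACE between the two groups the trial will be stopped (one-sided test, alpha = 0.05".

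The article does not define the safety population further. It does not say whether interim groups follow the allocation or the treatment received.

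**The concern.** The interim test is not a descriptive safety table. It is a formal comparison of the primary composite, read at six rather than 12 months, and a significant result ends the trial. It would be expected to use the set that protects the primary result, namely all randomised patients in their allocated arms. Instead it uses a treated population, next to a reference to the actual treatment group.

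If groups are formed by treatment received, any patient who moves between groups for reasons linked to prognosis biases the comparison. The trial could then stop on a difference that the intention-to-treat analysis would not show, and an early stop cannot be undone.

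A second, separate matter is the quantity tested. It is called a proportion at six months, yet the denominator includes patients enrolled shortly before the look. The Follow-up section schedules visits at 1 and 12 months and none at six, so a plain six-month proportion has no scheduled contact behind it either.

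**Working it through.** **Inputs from the article.** 12-month MACE of 20% v 10%; two-sided 5%, 80% power; 197 per arm; 414 in total; 1:1 allocation; enrolment over 3 years; interim look six months after the 150th patient; one-sided Fisher exact test at 0.05.

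**Assumptions (not in the article).** Constant hazard, even accrual, 75 per arm among the first 150, and the crossover shares and risk ratios below.

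**1. The plan's own figure.** With unpooled variance, n = (1.96 + 0.84)² × (0.2×0.8 + 0.1×0.9) / 0.1² = 196.2, so 197 per arm. For 5% loss, 394/0.95 = 414.7, stated as 414. The design figures reproduce.

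**2. Six-month risks.** 1 − √0.8 = 10.6% and 1 − √0.9 = 5.1%, a gap of 5.4 points before rounding.

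**3. Test by randomised arm, 75 per arm.** Exact enumeration of the Fisher test with 10.6% in both arms gives a 3.1% chance of stopping in favour of complete revascularisation. Under the design effect (10.6% v 5.1%) the chance of stopping is 25%.

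**4. Test by treatment received, no true effect.** Let x of the 75 complete-arm patients be reclassified to usual care, with g = x/75 and RR times the risk of those who stay. The arm average is held at 10.6%.

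- Risk in those who stay: lo = 0.106 / (1 − g + g×RR)
- Risk in the enlarged usual-care group: (75×0.106 + x×RR×lo) / (75 + x)

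Example with x = 8, RR = 2: lo = 0.106/1.107 = 9.6%; usual care = (7.95 + 8×0.192)/83 = 11.4%. A gap of 1.8 points appears with no treatment effect.

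Chance of a false stop in favour of complete revascularisation:

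| Reclassified (of 75) | RR 1 | RR 1.5 | RR 2 | RR 3 |
|---|---|---|---|---|
| 4 (about 5%) | 3.0% | 3.7% | 4.6% | 6.6% |
| 8 (about 10%) | 2.6% | 4.0% | 5.7% | 10.0% |
| 11 (about 15%) | 2.4% | 4.2% | 6.5% | 12.4% |
| 15 (20%) | 2.4% | 4.8% | 7.9% | 16.0% |

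The reference by randomised arm is 3.1%. The table uses the first 150 patients only.

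**5. Short follow-up.** Accrual is 414/36 = 11.5 per month. The 150th patient enters at 150/11.5 = 13.0 months and the look falls at 19.0 months. By then 6 × 11.5 = 69 more have entered, so 69 of 219 (32%) have under six months of follow-up. Averaged over 0 to 6 months of follow-up, their risk is 5.4% v 2.6%. Taking 110 per arm, 75 with full and 35 with partial follow-up:

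- Usual care: (75×10.6% + 35×5.4%)/110 = 8.9%
- Complete revascularisation: (75×5.1% + 35×2.6%)/110 = 4.3%

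With groups as randomised, the false-stop probability in one direction stays at 3.1%. The chance of stopping under the design effect goes from 25% (75 per arm) to 29% (110 per arm).

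**The case against.** The strongest reply is that grouping by treatment received is not stated. The sentence on the actual treatment group says that it is unblinded to the independent statistician, which may mean only that the statistician is told the arms. This stands: a reader may infer that the trial will be stopped on an as-treated comparison, but the article does not establish it. What remains is that the sentence sits beside a safety population of treated patients and nothing says that groups are as randomised. An unseen analysis plan does not settle this, because the article itself names a set other than the primary one.

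Secondly, the obvious crossover examples are largely care that the protocol allows within each arm. A second procedure for complex lesions belongs to the complete-revascularisation strategy, and staged non-culprit PCI within 6 weeks is a usual-care option. Neither patient has left the allocated strategy. This also stands, and it limits the likely number of reclassified patients. It does not remove the risk where a planned second procedure does not take place, or where treatment received is coded by procedure and not by strategy.

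Thirdly, randomisation follows successful culprit PCI in the same session, so the restriction to treated patients may exclude very few.

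Fourthly, a reader might infer that counting patients with short follow-up makes the comparison non-randomised or inflates false stopping. The calculation does not support that: both arms are affected alike and the false-stop rate is unchanged. Nor does it lose power relative to testing the first 150 alone.

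**Conclusion.** The point holds in a conditional form. On the face of the text, the rule that can end the trial uses a different population from the primary analysis and leaves open how its groups are formed. If they follow treatment received, the stopping comparison loses the protection of randomisation.

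How much that matters cannot be fixed from the article, which gives neither a crossover rate nor the risk of crossovers. With 5–20% reclassified there is no inflation at average risk (2.4–3.0% against 3.1%). At 1.5 times the risk the figure is 3.7–4.8%, still under the rule's nominal 5%. At twice the risk it is 4.6–7.9%, and at three times 6.6–16.0%. These figures assume one-way reclassification, constant hazard and 75 per arm.

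The handling of short follow-up is a lesser defect. The tested quantity is not a six-month risk (about 8.9% v 4.3% instead of 10.6% v 5.1%) and follow-up time is ignored, but false stopping does not rise.

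**What to change.** Reword the Interim analysis section, and the monitoring board's charter to match, so that:

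1. the MACE stopping comparison is made between the arms as randomised, in all patients randomised by the data cut;
2. it uses the log-rank test, or the difference in Kaplan-Meier estimates at six months, with patients censored at last contact. Both methods are already named in the statistical section of the article;
3. any table by treatment received is descriptive safety information for the monitoring board and plays no part in the stopping rule.

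The cost is a change of wording and slightly more analysis work. No new data are needed beyond each patient's event status and last contact date at the data cut, which a six-month proportion would need in any case.

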## Methods

### Study design

The South Limburg Myocardial Infarction (SLIM) trial is an investigator-initiated, multicentre, prospective, randomised clinical trial in non-STEMI patients with multivessel coronary artery disease amenable to treatment with PCI, in which 414 consecutive patients will be randomised in a 1:1 fashion, after completion of a successful culprit lesion PCI. In the IRA-PCI the identification of the culprit vessel will be performed according to electrocardiographic, echocardiographic and angiographic parameters as stated in the ESC guidelines [24]. The use of anatomic (intravascular ultrasound or optical coherence tomography) or functional (FFR) imaging modalities to assess the culprit lesion, or to rule out other mechanisms such as dissection or haematomas, will be left to the operator’s discretion. A patient will be excluded if the culprit artery is uncertain. Radial access will be strongly recommended for performance of coronary angiography and PCI.

All patients from June 2018 who present with at least one lesion with a stenosis of approximately 50% or more in a non-IRA with a diameter of ≥2.0 mm and fulfil the inclusion and exclusion criteria will be enrolled. Inclusion and exclusion criteria are listed in Tab. 1. The estimated duration of enrolment is 3 years. An overview of the trial is presented in Fig. 1.

**Table 1 Tab1:** Inclusion and exclusion criteria

Inclusion criteria	Exclusion criteria
Age between 18 and 85 years	Left main coronary artery disease (stenosis >50%)
Presenting with non-STEMI, to be treated with PCI of culprit lesion	Chronic total occlusion of a non-IRA
Presence of at least one stenosis of >50% in a non-IRA on QCA or visual estimation of baseline angiography	Complicated IRA treatment, e.g. extravasation, permanent no reflow after IRA treatment (TIMI flow 0–1) and inability to implant a stent
Non-IRA stenosis amenable for PCI treatment (operator’s decision)	Indication for or previous coronary artery bypass grafting
Able and willing to give signed informed consent	Known severe cardiac valve dysfunction requiring surgery or TAVI in follow-up period
	Killip class III or IV during completion of culprit lesion treatment
	Uncertain culprit lesion
	Life expectancy of <1 year
	Intolerance to aspirin, clopidogrel, prasugrel, ticagrelor or heparin
	Gastrointestinal or genitourinary bleeding in previous 3 months

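### The interim stopping rule uses one-sided 0.05 without naming a direction or protecting the final two-sided 5% test; if it can stop for benefit, false claims of benefit rise from 2.5% to about 4–5%

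*Protocol article*

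**What the plan says.** Under Sample size calculation and statistical power analysis, the protocol article sets the design level: "On the basis of a two-sided test size of 5% and a power of 80" per cent. The assumption is "we assume the incidence of MACE to be 20% in the IRA-PCI group and 10% in the ischaemia-driven MV-PCI group", from which "a minimum of 197 patients is needed to be recruited in each group to detect a 10% difference in the incidence of MACE at 1" (that is, at 12 months). The total follows: "To account for 5% loss to follow-up, a total of 414 (394/0.95) patients will be recruited". Intervals for the primary endpoint are at 95%, with no mention of adjustment for an earlier look.

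Under Interim analysis, the timing is given as "An interim analysis will be performed 6 months after 150 patients have been included", and "All patients who are accrued and treated will be included in the analysis". The analysis uses the safety population. The test is a one-sided Fisher exact test on the proportions with events at 6 months, and the rule given to the monitoring board is: "If there is a significant difference in MACE between the two groups the trial will be stopped (one-sided test, alpha = 0.05"). Nothing states which arm must do worse, whether the stop is for benefit or for harm, or how alpha is shared between the interim and final tests.

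**The concern.** Three features of the rule cause the difficulty.

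- **Direction.** A one-sided test needs a named direction. The trigger is worded as a difference between the groups, which fits either one. The board cannot derive a single p-value from the rule as written.
- **Level.** A two-sided 5% design allows 0.025 on each side. The interim rule uses 0.05 on one side, so the bar is lower at the early look than at the end.
- **Allocation.** The sample size uses the full two-sided 5% for the 12-month test and keeps nothing for the interim.

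If a benefit result can stop the trial, the superiority claim no longer has its stated error rate. The trial could also end on a handful of 6-month events, with an inflated effect estimate and no adequately powered 12-month comparison.

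**Working it through.** **1. The plan's own figure.** With 20% v 10%, two-sided 5% and 80% power (unpooled variance):

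n = (0.20×0.80 + 0.10×0.90) × (1.960 + 0.842)² / 0.10² = 0.25 × 7.85 / 0.01 ≈ 196.3, rounded up to 197 per group.

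This matches. 394/0.95 = 414.7, given as 414. A one-sided 5% test would need 157 per group by the pooled formula (199 for two-sided). The stated 197 therefore uses the whole two-sided 5%, with no interim allowance.

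**2. Size of the interim look.** Enrolment is estimated at 3 years (Study design), so 414/3 = 138 a year, or 69 in 6 months. With uniform accrual (an assumption), the look includes about 150 + 69 = 219 patients. It falls at about month 150/11.5 + 6 ≈ 19. Patients entered by about month 7, roughly 7 × 11.5 ≈ 80, already have 12 months of follow-up; the other 139 or so do not.

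**3. What it takes to stop.** With 75 per arm, one-sided Fisher gives p = 0.060 for 4 v 0 events and p = 0.029 for 5 v 0. Five events against none would stop the trial.

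**4. Error rates with the planned test.** Trials were simulated under the null with 12-month MACE of 10%, 15% and 20%, a one-sided Fisher test at the look and a two-sided 5% chi-square at 12 months. One model used uniform accrual, about 219 patients at the look and a constant hazard. The other fixed 75 or 110 per arm at the look, with 60% or 75% of the 12-month events occurring by 6 months.

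| Quantity under the null | Accrual model | Fixed-size model |
|---|---|---|
| Overall error, only benefit stops | 6.4–7.6% | 6.8–7.7% |
| Overall error, either direction stops | 8.3–10.4% | 8.8–10.5% |
| False claim of benefit, if benefit can stop | 4.0–5.2% | 4.4–5.2% |
| False claim of benefit, if harm only stops | not tabulated | about 2.5% |

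Fisher's test is conservative here: its actual size at the look is about 2.3–3.4% per direction. That alone takes nearly all, or more than all, of the 2.5% available on the benefit side.

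**5. Normal-theory upper figures.** With Z₁ and Z₂ bivariate normal, correlation √t and information fraction t = 0.20–0.36:

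- P(Z₁ > 1.645 or |Z₂| > 1.96) = 9.0–9.4%
- P(|Z₁| > 1.645 or |Z₂| > 1.96) = 13.1–13.7%

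**6. Behaviour under the planned effect.** With a constant hazard, 6-month risks are 1 − √0.80 = 0.106 and 1 − √0.90 = 0.051, a ratio of 0.49. In the accrual model a benefit stop occurs in about 29% of trials, on about 15 events, with a mean observed risk ratio of about 0.24. In the fixed-size model the stopping probability is 28–48%.

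**7. Effect of a strict boundary.** With an interim boundary of two-sided p<0.001 and the final test at two-sided 5%, overall error is 5.04% at t = 150/414 = 0.36 and 5.02% at t = 219/414 = 0.53. It is about 5.05% at smaller fractions.

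**The case against.** The strongest reply is that this is a safety look. It runs on the safety population, the rule is addressed to a safety monitoring board, and a one-sided test suits a search for harm. Under that reading the false-superiority rate stays near 2.5% and the final test needs no adjustment. This stands as a possible reading, so a reader who infers that the trial's false-positive rate certainly exceeds 5% goes further than the document supports. The text does not limit the rule to harm, however: it refers to a difference between the groups in MACE, the efficacy composite.

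Other stronger readings also fail:

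- **The rule contradicts itself.** It omits a direction. That is ambiguity, not contradiction.
- **No 12-month data would exist at the look.** On the accrual assumed above, about 80 of 219 patients would have them. The accurate statement is that most would not.
- **Overall error is 9–14%.** That is normal theory. The plan specifies Fisher's test, which gives lower figures.

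It is also fair to say that the article states no separate level for the final test; 5% is read from the sample size and the 95% intervals. An unseen analysis plan or monitoring charter might say more. That helps only in part. The protocol itself fixes the interim level, and at nominal one-sided 0.05 the benefit side has already exceeded 0.025, so no adjustment of the final test could recover it. A later document could settle the direction, but the sentence in the protocol would still need to change.

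**Conclusion.** The point holds in conditional form. The rule names no direction and leaves the final test unprotected. If it can stop for benefit, false claims of benefit rise from 2.5% to about 4–5%. Overall error is then about 6.5–7.5% (benefit only) or about 8.5–10% (either direction), with about 9% and 13–14% as normal-theory upper figures. Under the planned effect, nearly three trials in ten would stop early with a risk reduction well beyond the true one. If the rule is for harm only, the superiority claim is not inflated, and the defect is that the direction is unstated.

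The sizes rest on assumptions the article does not give: null 12-month MACE of 10–20%, uniform accrual, and a constant hazard or a 60–75% share of events by 6 months. The missing direction and the missing alpha allocation do not depend on them. The matter should be settled before the interim data are unblinded, because a direction chosen afterwards would not be credible.

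**What to change.** Rewrite the stopping rule in the Interim analysis section so that it names the direction, and carry the same text into the analysis plan and monitoring charter. There are two ways to do this.

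- **(a) Harm check.** Declare the look a one-sided test for excess MACE in the complete revascularisation arm, with no efficacy claim possible from it. The final two-sided 5% and the 414 patients then stand.
- **(b) Benefit stop.** If early stopping for benefit is wanted, use a Haybittle-Peto boundary (p<0.001) or an O'Brien-Fleming-type alpha-spending boundary at the actual information fraction, applied to benefit only. With p<0.001 the overall error is about 5.05% and 414 patients can stay. An alpha-spending boundary lowers the final level slightly (about 200–203 per group against 199 by the pooled formula, in the form checked). State a separate harm rule alongside it. If p<0.001 also governed harm, about 11 v 0 events at 75 per arm would be needed instead of 5 v 0, which would greatly weaken harm detection.

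The change is one paragraph in each document. The cost is a smaller chance of stopping early for benefit, and no such chance at all under (a).

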## Trial coordination

An independent Clinical Trial Centre will monitor the SLIM trial. The study monitor will visit each site at appropriate intervals to review investigational data for accuracy and completeness and ensure compliance with the protocol.

The study will be overseen by a trial steering committee and an independent Data and Safety Monitoring Board will review the clinical outcome data.

## Conclusion

The SLIM trial is a prospective, multicentre, 1:1 randomised controlled trial in which 414 patients with non-STEMI and MVD will be included. The study aims to provide evidence whether FFR-guided complete revascularisation by PCI is superior with respect to clinical outcomes compared to usual care in non-STEMI patients with MVD.
